#### Caregivers’ reports of understanding

The participating caregivers will answer an electronic questionnaire on their understanding of the patient and how the caregivers’ level of uncertainty (Table 3). After the study, the caregivers will answer how HR monitoring has affected their understanding of the patient.

**Table 3 Tab3:** Perceived understanding of the patient, questionnaire^a^

**Questions given at beginning and end of study period**	Predicted change at end of study period
Factor 1: The caregiver’s understanding of the patient	
When the patient is in pain or feels discomfort, I notice it	**↑**
I notice when the patient is happy	**↑**
When the patient is angry or irritated, I notice it	**↑**
I notice it when the patient is afraid	**↑**
I notice when the patient is sad	**↑**
Factor 2: The patient's ability to express	
The patient can tell me that he/she feels pain or discomfort	**↑**
The patient can tell me that he/she is happy	**↑**
The patient can tell me that he/she is angry	**↑**
The patient can tell me that he/she is afraid	**↑**
The patient can tell me that he/she is sad	**-**
Factor 3: The caregiver's emotional experiences	
I feel unsure whether I have understood the user	**↓**
I feel a sense of mastery because I understand the user	**↑**
I feel stressed because I don't understand the user	**↓**
I feel fear because I don't understand the user	**↓**
**Questions only included in survey given at the end of the study**	
Relative to before this study, how has your communication with the patient changed? Relative to before this study, how has your way of working with the patient changed? How satisfied are you with using HR as a means of communication? How satisfied are you with using the program for situational analysis? In general, how satisfied are you overall with system used in the trial? How often did you experience the “beep” of the HR increase to be useful, and how often not to be? What is the biggest roadblock for continuing use of the system in this study?	

^a^The questionnaire was developed in the autumn of 2020, in collaboration with [name], [name]. The questionnaire was based on a review of relevant literature, our own experience, and through discussion within the research group. The questionnaire was tested in a pilot study with 17 participants to perform an exploratory factor analysis. The modified questionnaire was distributed to 135 professional caregivers in 2021, and formed the basis of [name] et al., 2023 (in preparation). Each item in factor 1, 2 and 3 is answered on a Likert scale ranging from “never” to “always”. The hypothesis is that the sum score for questions on communication will increase after HR use

Questions only included in survey given at the end of the study are based on surveys for health technology satisfaction [91]

The questionnaire is trial specific and based on a review of relevant literature, experience working with the ID population, and discussion within the research group. The questionnaire was tested in a pilot study with 17 participants to perform an exploratory factor analysis for improved psychometric properties. The then-modified questionnaire was distributed to 135 professional caregivers in 2021 [90]. Confirmatory factor analysis indicates good model fit [90].

### Strategies to improve adherence to interventions

#### Measures of treatment compliance

Professional caregivers will be asked to what extent they, due to unplanned events, ended up missing registrations or deviating from the intervention protocol. Before every shift, the caregiver will have to sign a compliance to the intervention protocol, which also operates as a reminder for registrations. The leading caregiver will remind staff of the protocol at every shift meeting. Furthermore, all HR-increases are recorded automatically, and in addition the caregiver will be probed for contextual data for each HR-increase. The discrepancy between number of HR increases and number of contexts recorded gives us a measure of caregiver responsiveness.

### Data collection and management

#### Data management procedures

Participants will not be identified by name in the study database or on any study documents to be collected but will be identified by a site number, participant number, and initials. The principal investigator (Table 2) is responsible for all information collected on participants enrolled in this study. All data collected during this study must be reviewed and verified for completeness and accuracy by the principal investigator.

The data will be entered into Services for sensitive data (TSD): https://www.uio.no/english/services/it/research/sensitive-data/, an enclosed electronic storage system at the University of Oslo. All access to this database are strictly regulated. Only de-identified data will be shared with project team.

All procedures for the handling and analysis of data will be conducted using good computing practices meeting guidelines for the handling and analysis of data for clinical trials.

#### Data quality control and reporting

All changes to the study database will be documented.

#### Archival of data

The database is safeguarded against unauthorized access by established security procedures; appropriate backup copies of the database and related software files will be maintained. Databases are backed up by the database administrator in conjunction with any updates or changes to the database.

#### Statistical methods and considerations

Statistical analyses are performed using SPSS version 25 [92] and R Studio [93].

#### Demographic and baseline characteristics

The following demographic variables at screening will be summarized: gender and age, height, and weight (for the calculation of body mass index). Descriptive analyses will consist of means and SD for continuous variables and percentages for categorical variables.

#### Analysis of primary objectives

We hypothesize that a 2 SD increase in HR can identify potentially painful care situations that require re-evaluation. To determine whether HR monitoring is effective in identifying situations that require changes in care, we will compare the mean HR spike counts between situations that are suitable for adjustments in care versus situations that are not. If Shapiro–Wilk test show normality of data distribution, we will use a one-tailed paired sampled t-tests; if non-normality is indicated we will use the Wilcoxon signed-rank test.

The potential for HR to identify potentially painful care procedures will also be shown as descriptions of identified situations and shown as a number count (primary hypothesis). All situations identified by 2 SD increase in HR will be described and reported as count, including an overview of number of times each of the different situations were accompanied by increases in HR (reproducibility); number of HR increases with no registration (responsiveness of caregiver); number of HR increases recorded in situations not previously thought to entail pain or distress (novel discoveries); number of situations discovered through HR-use during the registration phase where instantaneous changes were made due to obvious acute pain (e.g. skin pinched while putting on cast; instantaneous clinical effect of HR); and number of situations identified that were available for adjustments in care and systematic evaluation (formal clinical applicability of HR).

#### Analysis of secondary objectives

To test evaluate the effect of using HR in improving care procedures and reducing pain, one-tailed paired samples t-tests are used to test for difference in HRV and cytokine biomarkers (MCP-1, IL-1RA, IL-8, TGFβ1, and IL-17) before and after intervention (secondary hypothesis 1). Cohen’s *d* values [94] will also be calculated to determine the size of the effect. To evaluate the effect of HR-informed changes in procedures, differences in biomarker scores across the early and delayed groups will be analysed using Wilcoxon Signed-rank test, which can evaluate whether the difference scores from each group are not equal (i.e., that they are significantly different). Critical P-values for the five cytokine measurers will be corrected for multiple comparisons using a 5% false discovery rate [95].

To test for significant change in rates of understanding the patient throughout study period (secondary hypothesis 2), we will perform one-tailed paired sampled t-tests. Additionally, Spearman’s rank-order correlation (*r*_s_) is used to investigate relationships between HR measures and caregivers report on NCPC and caregivers report on perceived understanding of the patient.

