## Methods

### Study design overview

This is a single centre, controlled, randomized trial with 38 non-verbal participants, testing if HR-guided interventions in suspected painful settings will change the incidence of pain. The study design includes a two-week *pre-intervention*, consisting of continuous HR registering across four potentially painful settings; and an *intervention phase* consisting of formal change in procedure for the identified painful situation (Fig. 1). The interventions are in one of four forms: changes in 1) physiotherapy techniques, 2) preparations for putting on casts, 3) lifting techniques or 4) personal hygiene procedures. HRV and inflammatory cytokines (MCP-1, IL-1RA, IL-8, TGFβ1, and IL-17) are measured at the beginning, midway, and end of the study period to assess change in long-term pain. Participants will be randomly assigned to either an early intervention group or a delayed intervention group in a 1:1 ratio using a computer-generated randomization scheme. This will differentiate the effect of formal change in routine from increased attentiveness due to study participation, and instant changes made when the HR band signify obvious acute pain (such as skin pinched while putting on a cast). Overview over measures and objectives is given in Table 1.

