The ethical implications of this study are complex, particularly regarding the patients’ inability to provide informed consent. The mentioned issue of the caregiver as an intermediary is relevant to the ethical considerations taken when designing the study. An apparent way to bypass the intermediary of the caregiver would be to use video recording in addition to HR. However, HR is generally regarded as less intrusive than video recording and considered more ethically just [97]. If video recordings of caregivers were to be conducted, it would be necessary to obtain informed consent from every caregiver involved, as well as any non-participating patients present in the facility. This would introduce additional ethical considerations related to the proper treatment of human subjects in research. We believe HR is informative yet acceptable, a non-invasive technology, possibly of great beneficence to the patients. Another ethical concern here is the aspect of delayed intervention. Obvious painful situations will be detected during the registration phase, and it is not ethical to postpone making changes in these routines for two or four weeks. This ethical aspect makes for more challenging methodology. However, as these instantaneous adaptations are registered, as well as having a delayed intervention group, results will still be valid for evaluation of HR as a communicative aid.

In conclusion, this trial is a randomized blinded controlled clinical trial that test the applicability of HR to reduce incidence of pain in the participant’s everyday life. We will evaluate how HR can be used to identify potentially painful care procedures that should be re-evaluated in terms of the approach taken; test the effect of HR-informed changes in potentially painful care procedures on biomarkers of pain; and assess how six weeks of communication through HR affects the quality of communication between patient and caregiver. Regardless of outcome, the current study will advance the field of wearable physiological sensor-use in patient care.

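### Secondary hypothesis 1 is tied to an uncontrolled one-tailed before-after test, with no precedence for the randomised comparison, and secondary hypothesis 2 has no control at all

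*Protocol article*

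**What the plan says.** All references are to the protocol article.

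**Purpose of the delayed arm.** Study design overview says of the random allocation: "This will differentiate the effect of formal change in routine from increased attentiveness due to study participation". The same sentence extends this to immediate changes made when the HR band signals obvious acute pain. The Abstract and the section on assigning participants to groups give the same purpose.

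**Hypothesis 1.** Analysis of secondary objectives states that "one-tailed paired samples t-tests are used to test for difference in HRV and cytokine biomarkers" (the five cytokines are listed), and the sentence ends "before and after intervention (secondary hypothesis 1"), so the hypothesis label sits on the before-after test. It then adds that "differences in biomarker scores across the early and delayed groups will be analysed using Wilcoxon Signed-rank test", introduced as evaluating the effect of the HR-informed procedure changes. The section does not say which analysis decides the hypothesis or over which interval the difference scores are taken.

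**Hypothesis 2.** The same section says: "To test for significant change in rates of understanding the patient throughout study period (secondary hypothesis 2), we will perform one-tailed paired sampled t-tests". No comparison between arms is planned. The Table 3 items are headed "Questions given at beginning and end of study period", and Table 1 places the survey in weeks 1 and 6.

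**Claim.** The Discussion argues that, because instantaneous adaptations are registered, "as well as having a delayed intervention group, results will still be valid for evaluation of HR as a communicative aid".

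**The concern.** The protocol itself expects non-specific change from monitoring, caregiver attention and immediate adaptations, and it randomises the timing of the procedure change to separate these out. A before-after test cannot make that separation. It counts any favourable movement between the two samples, whatever its cause, and a one-tailed version rewards movement in that direction only.

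For hypothesis 1, a positive before-after result could be reported as support even if the randomised comparison showed nothing, because no order between the two is fixed. For hypothesis 2, the outcome is rated by caregivers who see the HR alerts and know what the study hopes to find. No planned contrast separates HR use from time, attention or expectation. These two hypotheses carry the trial's claims about effect on pain biomarkers and on communication, in a trial that its Discussion presents as randomised and controlled.

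**Working it through.** **1. Exposure against measurement** (Table 1; Intervention; Method of assigning participants to treatment groups)

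| Weeks | Early arm | Delayed arm | Biomarkers | Questionnaire |
|---|---|---|---|---|
| 1–2 | HR alerts | HR alerts | week 1 | week 1 |
| 3–4 | HR alerts + procedure change | HR alerts | week 4 | none |
| 5–6 | HR alerts + procedure change | HR alerts + procedure change | week 6 | week 6 |

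Three things follow.
- The early arm has no sample at the end of week 2, so its before value precedes two weeks of alerts and informal adaptations.
- The arms differ in exposure only in weeks 3–4. Change from week 1 to week 4 is therefore the clean randomised contrast. Change from week 1 to week 6 compares four weeks of procedure change with two, and its expected difference is zero if the effect plateaus by two weeks.
- At both questionnaire times the arms have the same HR status, and by week 6 both are in the procedure-change phase. No between-arm contrast of these data can isolate HR use.

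**2. The plan's own figure.** Sample size gives d = 0.84 for a one-sided paired t-test with 38 patients, 80% power and alpha 0.05. The Fig. 3 legend gives 0.82.

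Paired power = 1 − F(t₀.₉₅,ₙ₋₁; df = n − 1, ncp = d√n), where F is the noncentral t distribution.
- n = 38, d = 0.84: ncp = 0.84 × 6.164 = 5.18, power 99.97%. The effect detectable with 80% power is d = 0.41, so the stated figure does not reproduce as a paired test.

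Two-sample power uses df = 2m − 2 and ncp = d√(m/2), with m per arm.
- m = 19: √9.5 = 3.082. Power is 79.8% at d = 0.82 and 81.5% at d = 0.84, and the detectable d is 0.822.

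The stated effect sizes therefore match a comparison of 19 against 19, which is the randomised contrast. That the text calls it paired is a separate defect.

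**3. Before-after test with no intervention effect.** Assume a favourable non-specific shift δ, in SD of the paired differences. The document gives no such figure, so a range is shown. The rejection rate is the paired formula with d = δ. Completers: 38 × 0.85 = 32.3, taken as 32. Critical t is 1.687 (n = 38) and 1.696 (n = 32).

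| δ | ncp, n = 38 | Rejects | ncp, n = 32 | Rejects |
|---|---|---|---|---|
| 0 | 0 | 5% | 0 | 5% |
| 0.1 | 0.616 | 15% | 0.566 | 14% |
| 0.2 | 1.233 | 33% | 1.131 | 30% |
| 0.3 | 1.849 | 57% | 1.697 | 51% |
| 0.4 | 2.466 | 78% | 2.263 | 72% |
| 0.5 | 3.082 | 92% | 2.828 | 87% |

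These rates are for a single test without multiplicity correction.

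**4. Sensitivity of the randomised contrast** (one-sided, alpha 0.05, 80% power)

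| Test | Full sample | After 15% dropout |
|---|---|---|
| Two-sample t, 19 or 16 per arm | d = 0.82 | d = 0.90 |
| Rank-sum (relative efficiency 3/π), 19 or 16 per arm | d = 0.84 | d = 0.92 |
| Pooled paired t, n = 38 or 32 | d = 0.41 | d = 0.45 |

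The paired d is in SD of the within-patient change. The two-sample d is a difference between arms in SD of the change score.

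**5. The named between-arm test.** The signed-rank test needs pairs, and two independent arms of 19 have none. In 4,000 simulated trials with arbitrary pairing, type I error was 5.1% (rank-sum 4.8%), and power at d = 0.82 was 75% (rank-sum 77%). The fault is that the result depends on how patients happen to be matched. Gross error inflation is not the problem.

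**The case against.** A reader might infer that both secondary hypotheses ignore the delayed arm. The document does not support that for hypothesis 1: an early-versus-delayed comparison of biomarker difference scores is planned straight after the before-after tests, and its stated aim nearly repeats the first secondary objective. Nor does the text say that the before-after test alone decides. It attaches the hypothesis label to that test and ranks neither.

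Further points on the other side:
- The before-after test is introduced as addressing the wider effect of using HR to improve care, for which informal adaptations are part of the effect. This is fair, but attention, time and habituation to sampling remain mixed in. Hypothesis 1 itself is worded in terms of changes to care procedures.
- Ranking two secondary analyses could be left to an analysis plan. That is true of a mere gap. Here the label already sits on the uncontrolled test.
- The shifts in the illustration are assumed, and drift could be unfavourable: the ethics section notes that the monitor may provoke and blood sampling may hurt. Unfavourable drift would make the one-tailed test conservative. The 5% false discovery rate across the five cytokines means the rates do not carry over to them directly. Some patients may have no procedure change, so n = 38 or 32 is an upper bound. All of this stands.
- The Discussion's claim rests on registering adaptations as well as on the delayed arm. This also stands, but registration supplies no comparator without HR.
- Hypothesis 2 is openly defined as change from start to end. Yet it is worded as an increase caused by the HR aid.

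**Conclusion.** The concern holds in this form. For hypothesis 1, the labelled test is uncontrolled and one-tailed, and its early-arm baseline precedes two weeks of the very effects the delayed arm was added to separate. The controlled comparison exists, but it lacks precedence, an interval and a test suited to independent arms. For hypothesis 2, no comparator without HR exists at either measurement, so the Discussion's statement that results remain valid for evaluating HR as a communicative aid is not a property of this design. A different test would not repair that.

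The 33% to 78% at n = 38 (30% to 72% at n = 32) illustrates what a favourable drift of 0.2 to 0.4 SD would do to one uncorrected test. It does not estimate the trial's error rate, because the size and direction of any drift are unknown. The argument from the timetable needs no such assumption.

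**What to change.** **Hypothesis 1.** State that the between-arm comparison of change from baseline to the week 4 sample, taken before the delayed arm's procedure change, decides the hypothesis. Replace the signed-rank test with one for independent groups: a rank-sum test, or a model of the week 4 value adjusted for baseline. Keep the false discovery rate step for the cytokines. Report before-after changes by arm as descriptive. Reconcile the mid-study timing, since Table 1 shows week 4 and the Fig. 2 legend says the end of week 3.

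**Hypothesis 2.** Present it as descriptive, uncontrolled change within caregivers, and remove the Discussion's validity claim for it. Optionally, give the electronic questionnaire at mid-study too. That would allow a randomised comparison of the formal procedure change on perceived understanding, though still not of HR use.

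**Cost.** The required changes are wording and choice of test, and the samples are already scheduled. The loss is sensitivity, as shown under the randomised contrast above: detectable d of about 0.82 (19 per arm) to 0.90 (16 per arm), against 0.41 to 0.45 for the pooled paired test. The trial's stated effect sizes already correspond to the two-arm comparison. The optional questionnaire adds one short survey per caregiver.

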**Methods:**

We will recruit 38 non-communicative patients with autism and ID residing in care homes. *Assessments*: HR is measured continuously to identify acutely painful situations. HR variability and pain-related cytokines (MCP-1, IL-1RA, IL-8, TGFβ1, and IL-17) are collected as measures of long-term pain. Caregivers will be asked to what degree they observe pain in their patients and how well they believe they understand their patient’s expressions of emotion and pain. *Pre-intervention:* HR is measured 8 h/day over 2 weeks to identify potentially painful situations across four settings: physiotherapy, cast use, lifting, and personal hygiene. *Intervention:* Changes in procedures for identified painful situations are in the form of changes in 1) physiotherapy techniques, 2) preparations for putting on casts, 3) lifting techniques or 4) personal hygiene procedures. *Design:* Nineteen patients will start intervention in week 3 while 19 patients will continue data collection for another 2 weeks before procedure changes are introduced. This is done to distinguish between specific effects of changes in procedures and non-specific effects, such as caregivers increased attention.

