#### Method of assigning participants to treatment groups

The study design employs an early and a delayed intervention group to distinguish the effects of formal routine changes from increased attentiveness due to study participation and effects of instantaneous changes in care. The early intervention group will start intervention in week three while the delayed group will continue data collection for another two weeks before introducing procedure changes. Patients will be randomly assigned to one of the two groups (Fig. 1) on a 1:1 ratio using a computer-generated randomization scheme.

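### The early-versus-delayed comparison is given the Wilcoxon signed-rank test, a paired test that does not fit two independent randomised groups

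*Protocol article*

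**What the plan says.** The Methods paragraph of the abstract describes two parallel groups: "Nineteen patients will start intervention in week 3 while 19 patients will continue data collection for another 2 weeks before procedure changes are introduced". It gives the reason: "This is done to distinguish between specific effects of changes in procedures and non-specific effects, such as caregivers increased attention". Under Method of assigning participants to treatment groups, the allocation is stated as "Patients will be randomly assigned to one of the two groups (Fig. 1) on a 1:1 ratio using a computer-generated randomization scheme". No section mentions matching or pairing of patients across groups.

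Analysis of secondary objectives contains two separate analyses of the biomarkers:

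- Within patients, before versus after: "one-tailed paired samples t-tests are used to test for difference in HRV and cytokine biomarkers".
- Between groups: "differences in biomarker scores across the early and delayed groups will be analysed using Wilcoxon Signed-rank test". The test is described as one "which can evaluate whether the difference scores from each group are not equal".

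The signed-rank test also appears under Analysis of primary objectives, as the fallback for a paired t-test: "if non-normality is indicated we will use the Wilcoxon signed-rank test". No rank-sum test or other two-sample test is named anywhere in the article.

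**The concern.** The signed-rank test works on one set of differences, each formed within a patient or a matched pair. Across the two arms no such differences exist. The sentence describes a comparison between groups and then names a test that does not make one.

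The delayed group is there to separate the effect of formal procedure changes from extra attention and from ad hoc adaptations. The before/after paired t-tests cannot do that. The between-group comparison is therefore the only stated analysis that uses the randomisation, and secondary hypothesis 1 depends on it for any causal reading.

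The sentence also leaves open which difference score is meant. Table 1 shows both arms under changed procedures in weeks 5 and 6, so a baseline-to-end difference has no untreated comparator.

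**Working it through.** **Inputs from the article.** 19 early and 19 delayed patients (abstract). 15% dropout, one-sided alpha 0.05, 80% power (Sample size). Withdrawals not replaced (Replacement of participants). Biomarkers sampled at baseline, mid-study and end (Table 1; HRV monitoring of prolonged pain; Biochemical measurements).

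**Assumption.** The article gives no biomarker SDs, so change scores are simulated as normal with SD 1.

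**The plan's own power figure.** Sample size gives d = 0.84 and the Fig. 3 caption 0.82, both for a paired t-test with 38 patients. A one-sided paired test with n = 38 detects approximately (1.645 + 0.842)/√38 = 0.40 (exact, noncentral t: 0.41). A two-sample test at 19 versus 19 detects approximately 2.487 × √(2/19) = 0.81 (exact: 0.822). The stated figure is therefore in effect an independent-groups figure. That mismatch is a separate matter. It matters here only because the planned size already fits a two-sample test.

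**Ways the stated test could be run**

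1. *Arbitrary early–delayed pairs.*
   - One 19/19 data set with rank-sum p = 0.23, paired at random 5,000 times, gave signed-rank p from 0.008 to 0.74 (central 95%: 0.04–0.35). Four further data sets with the same rank-sum p gave minima of 0.006–0.029 and maxima of 0.62–0.83.
   - At a true difference of d = 0.82, re-pairing the same data once changed the verdict at one-sided 0.05 in about 10% of 2,000 simulated trials.
   - With independent 15% dropout, the chance of unequal arms is 1 − Σₖ b(k; 19, 0.85)² = 0.82, where b is the binomial probability of k completers. In about four trials in five, some patients could not be paired.

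2. *Within each arm, reading significance in the early arm only as an effect.* Dropout leaves 19 × 0.85 ≈ 16 per arm. With no arm difference and a drift shared by both arms (two-sided 0.05, 4,000 replicates):

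| Shared drift (SD) | Significant in early arm only | Rank-sum rejects |
|---|---|---|
| 0 | 4% | 5% |
| 0.1 | 6% | 5% |
| 0.2 | 9% | 5% |
| 0.3 | 15% | 5% |
| 0.5 | 24% | 5% |
| 0.7 | 20% | 5% |

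Independent runs put the 0.3–0.7 SD range at 14–26%.

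3. *On all 38 change scores pooled.* The test then ignores arm. With a shared change of 0.5 SD and no arm difference it rejects in 90% of trials (one-sided 0.05), against about 5% for rank-sum. It would report as a finding the non-specific effect that the design is meant to remove.

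**Which time point has a comparator.** Table 1 takes the mid-study biomarkers in week 4, when only the early arm has changed procedure. The HRV and biochemistry sections agree, placing them two weeks into the early group's intervention. The Fig. 2 caption instead puts the mid assessment at the end of week 3. The difference from baseline to the sample at the end of the early-only period is the one with an untreated comparator.

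**Efficiency of the replacement.** With baseline/follow-up correlation ρ, the variance ratio of ANCOVA to change scores is (1 − ρ²)/(2(1 − ρ)) = (1 + ρ)/2. That is 65%, 75% and 85% at ρ = 0.3, 0.5 and 0.7 (assumed values).

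**The case against.** The strongest reply has five parts.

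- **Error rate.** With equal arms and a pairing fixed in advance, the signed-rank test keeps its type I error near 5% and has almost the power of rank-sum (about 0.76 against 0.77 at d = 0.82). This is correct, so calling the test invalid in every use would be too strong. But the article specifies no pairing, the design offers none, and the result depends on row order.
- **Illustrative ranges.** The p-value range is the extreme over many pairings, and most pairings stay on the same side of 0.05. The figure of about 10% changed verdicts is the more representative one. The 14–26% needs a shared drift that the article does not state, and a within-arm reading that runs against the sentence's own purpose. These figures show what could happen; they are not predictions.
- **A slip for rank-sum.** This is plausible, but nothing in the text shows it. The same test is named correctly in the primary analysis, and the between-group purpose is spelled out beside the wrong name. A slip would need the same correction.
- **Time point.** The mid-study contrast can be inferred from the schedule, and an article may leave such detail to the analysis plan. That is fair on its own. Since the sentence must be rewritten, the time point should be stated in it, all the more because the Fig. 2 caption disagrees with Table 1.
- **Severity.** The analysis is secondary, and the primary analysis is unaffected. That is true, but no other stated analysis uses the randomisation.

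**Conclusion.** The concern holds. The article assigns a paired test to a comparison of two unmatched randomised groups. This is a wrong statement in the current text, not a detail left for later. As written, the result would depend on an arbitrary pairing (about 10% of verdicts change on re-pairing at d = 0.82), pairing would be incomplete in about 82% of trials with 15% dropout, or the arms would not be compared at all. The 82% assumes that patients drop out independently of one another. The other figures assume normal change scores with SD 1, and the within-arm and pooled figures also assume a shared drift; the article gives none of these quantities. The conclusion that the test does not fit the design needs none of them. It must be fixed before the data are analysed.

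**What to change.** Replace the sentence with a between-arm analysis: for HRV and each log-transformed cytokine, ANCOVA of the mid-study value on randomised arm and the patient's own baseline value, reporting the adjusted difference with a 95% confidence interval. If a rank test is preferred, use the Wilcoxon rank-sum (Mann–Whitney) test on baseline-to-mid-study changes, which is the smallest change that makes the sentence correct. State that mid-study means the sample at the end of the period in which only the early arm has changed procedure, and reconcile the Fig. 2 caption with Table 1. Apply the 5% false discovery rate across the five cytokines to these between-arm p-values.

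The cost is about two sentences of analysis text. The samples are already scheduled, so no new data are needed. A two-sample t-test at 19 versus 19 has 79.8% power at d = 0.82 (one-sided 0.05). With 16 versus 16 after dropout, the detectable difference rises to d = 0.90.
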